### Study design

SYNERGY is a single-centre, double-blind, placebo-controlled, randomised cross-over trial. Participants will undergo a 2 week run-in period, followed by randomisation to either synbiotic supplements or placebo for 6 weeks. Thereafter, participants will undergo a further 4 week washout period followed by crossover to the alternative intervention (Figure 1). The 4 week washout is considered sufficient for the pre-intervention microbiota to re-establish [19].

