### Randomisation

Computer-generated randomisation of participants to treatment order will be undertaken by an external statistical consultant. This process of allocation will conceal the randomisation order to researchers and participants. In addition, the supplements will be packed off-site with a generic label, supplement A or B, for the first and second intervention, respectively.

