### Supplement dosing and duration

The synbiotic intervention will be a daily dose of 15 grams of prebiotics, including a combination of 3 different types of fibres, and the probiotic component will include 90 billion colony-forming units (CFU) from 9 different strains across the Lactobacillus, Bifidobacteria and Streptococcus genus. There is no consensus as yet on adequate dosing or duration of synbiotics due to the diversity of GI survival rates of probiotic strains and the different characteristics of prebiotic varieties, such as their bifidogenic capacities [33]. Nevertheless, the available evidence suggests that there maybe be a threshold dose and duration required to see a benefit for lowering IS and PCS production [19]. The dosing of pre- and probiotics used in SYNERGY is based on previous successful trials [30,36,37]. However, in order to minimise the side effects reported in previous studies, such as flatulence and bloating [38], the synbiotics will commence at half dose for the first 3 weeks.

The durations of most intervention studies in this area have been ≤4 weeks, with one study demonstrating no benefit comparing 4, 8 and 12 week intervention periods [37]. The intervention period for SYNERGY is a 6 week duration to allow time for dose escalation, minimise symptom burden and establish whether there is a dose-dependent and sustained benefit of the therapy.

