#### Gastrointestinal symptoms

Monitoring GI symptoms in SYNERGY has two purposes, safety monitoring and hypothesis generation. The validated Gastrointestinal Symptom Rating Scale (GSRS) will be administered at baseline, mid-point (prior to dose escalation), and the end of each intervention [51]. The GSRS data will be presented as a total score and as dimension scores (reflux, pain, indigestion, constipation and diarrhoea) [52].

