### Statistical analysis

Preliminary data from a cohort of CKD Stage IV-V (pre-dialysis) patients recruited from the same Nephrology department were used for power calculations. The mean serum concentration of IS in this population was 14 μmol/L with a mean intra individual standard deviation of 4 μmol/L between 3 measurements over a 6 week period (unpublished data from [name] and [name]). With 1:1 randomisation, SYNERGY will require 24 participants to complete the study. This sample size is based on a 30% reduction in IS levels; alpha of 5% and power of 90%. Allowing for a 20% drop out and using the adjustment factor 1/1(1-υ)^2^, a total of 37 participants will be recruited. This magnitude of change is related to a significant improvement in kidney function [56]. Furthermore, a reduction in IS concentration of this size has been achieved in previous probiotic intervention studies and is therefore considered a realistic target [57].

The primary analysis of IS concentrations will be undertaken using an independent t-test with treatment sequence allocation as the independent variable and the difference between serum concentrations measured after the first and second treatment as the dependent variable [58]. Secondary analysis of the primary outcome will include mixed modelling to account for missing data and to determine whether there is a dose dependent effect of the synbiotics.

In addition to the widely used diversity metrics and analysis tools available via QIIME, permutational multivariate analysis of variance (PERMANOVA) will be conducted on the genus level operational taxonomic units (OUT) tables to test the relationships between the stool microbiome and the primary and secondary outcomes of the study. Constrained ordination methods, such as analysis with respect to instrumental variables, will also be carried out [59].

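### The planned test of dose dependence cannot separate dose from time on synbiotic, because every patient follows the same escalation schedule

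*Protocol article*

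**What the plan says.** The Statistical analysis section makes the end-of-treatment comparison of IS the primary analysis. As a secondary analysis of the same outcome it adds "mixed modelling to account for missing data and to determine whether there is a dose dependent effect of the synbiotics". The section Supplement dosing and duration gives a matching reason for the 6-week period: among other things, to "establish whether there is a dose-dependent and sustained benefit of the therapy".

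The schedule is set out in several places:

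- **Dose.** Supplement dosing and duration states: "The synbiotic intervention will be a daily dose of 15 grams of prebiotics", together with 90 billion CFU of probiotic. It adds that "the synbiotics will commence at half dose for the first 3 weeks".
- **Timing of escalation.** Table 2 marks dose escalation at the mid point. The Gastrointestinal symptoms section describes the symptom scale as given at "mid-point (prior to dose escalation" (closing bracket omitted), so the mid-point visit falls before the increase.
- **IS samples.** Table 2 lists baseline, mid point and end point at weeks 0, 3 and 6 of the first period and weeks 11, 14 and 17 for the second.
- **Randomised factor.** Randomisation: "Computer-generated randomisation of participants to treatment order will be undertaken by an external statistical consultant". Study design: "randomisation to either synbiotic supplements or placebo for 6 weeks". No second dose group is described.

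The dosing section also says there may be a "threshold dose and duration required to see a benefit for lowering IS and PCS production", so the authors themselves regard duration as a possible determinant of effect.

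**The concern.** A dose-response conclusion needs patients observed at different doses after the same time on treatment, or at the same dose after different times. This schedule gives neither. At 3 weeks on synbiotic the scheduled dose is always half, and at 6 weeks it is always the escalated dose. A difference between the two visits may come from the higher dose, from 3 further weeks of exposure, or from both.

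If the plan is followed as written, an effect that simply takes time to develop would be reported as dose dependence. The article says there is no consensus on dose or duration and hopes the results will help refine the formulation. A mistaken dose claim could therefore steer later work.

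**Working it through.** The plan states no figure for this analysis, so there is none to reproduce. The question is whether the two effects can be identified separately.

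**Step 1: line up dose and time.** Inputs are the half-dose start, escalation at the mid point and the IS visits in Table 2. Escalated dose is coded as 1.

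| Weeks on synbiotic | 0 | 3 | 6 |
|---|---|---|---|
| Scheduled dose | 0 | 0.5 | 1 |

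Dose = weeks / 6 at every visit. On placebo both are 0. Over all sequence, period and visit cells the correlation is exactly 1.

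**Step 2: check the rank of the cross-over design.** The design has 2 sequences, 2 periods and 3 visits. The base model has an intercept, sequence, period, two visit terms and two period-by-visit terms.

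| Model | Columns | Rank |
|---|---|---|
| Base | 7 | 7 |
| Base + dose | 8 | 8 |
| Base + dose + time on synbiotic | 9 | 8 |
| Base + treatment-by-visit contrasts at weeks 3 and 6 | 9 | 9 |
| The same + dose + time on synbiotic | 11 | 9 |

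Time on synbiotic adds nothing once dose is in the model. The two placebo-adjusted contrasts can be estimated; splitting them into dose and duration cannot. As a check on the method only, a hypothetical layout in which dose differed between randomised groups at the same week gave full rank, 9 of 9.

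**Step 3: show two truths that give the same data.** The Statistical analysis section uses a mean IS of 14 μmol/L and a 30% reduction: 0.30 × 14 = 4.2 μmol/L.

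- Pure linear dose effect: 0.5 × 4.2 = 2.1 lower at week 3; 1 × 4.2 = 4.2 lower at week 6.
- Pure duration effect of 0.7 μmol/L per week, dose irrelevant: 0.7 × 3 = 2.1 lower at week 3; 0.7 × 6 = 4.2 lower at week 6.

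The expected values agree at every visit, so more patients would not help.

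**Step 4: size of a spurious dose gain.** The documents give no onset rate. Assume that an effect independent of dose builds up as 1 − exp(−t/τ), with t and τ in weeks. The week-6 to week-3 ratio is (1 − exp(−6/τ)) / (1 − exp(−3/τ)) = 1 + exp(−3/τ).

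| τ (weeks, assumed) | Share of maximum, week 3 | Share of maximum, week 6 | Apparent gain |
|---|---|---|---|
| 1 | 95.0% | 99.8% | 5% |
| 3 | 63.2% | 86.5% | 37% |
| 6 | 39.3% | 63.2% | 61% |

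**The case against.** **The placebo period controls for time.** In part. It removes visit, calendar and period trends. Time on placebo is not time on synbiotic, though, so the onset and build-up of the synbiotic's own effect stay in the contrast.

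**Intake will vary between patients.** The Safety and adherence section records pill counts and powder weights at the mid point and end of each intervention. It would therefore go too far to say that the trial holds no information on dose; the aliasing concerns scheduled dose. But variation in intake is not randomised, may reflect tolerance and adherence, and is not named as the basis of the dose analysis.

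**The authors considered duration.** The dosing section cites a study that compared 4, 8 and 12 weeks and found no benefit. The sentence is ambiguous, and the shortest of those periods is already longer than 3 weeks, so it cannot rule out a change between weeks 3 and 6.

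**The model terms belong in a statistical analysis plan.** They do, and their absence is no fault here. What fails is the stated aim: no choice of terms separates scheduled dose from time under this schedule.

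**The aim of a sustained benefit.** A reader might infer that this fails too. It does under one reading, persistence at a constant dose, because IS is sampled only once per period after escalation. Read as an effect at week 3 that is still present at week 6, it can be estimated. The text does not force the first reading.

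**It is only a secondary analysis.** This stands. Dose dependence is not among the primary or secondary hypotheses under Study aim, and the trial describes itself as proof of concept.

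**Conclusion.** The point holds for scheduled dose. The plan promises to determine dose dependence, but dose and time on synbiotic are fully aliased, so a week-6 effect larger than the week-3 effect cannot be attributed to dose. This follows from the schedule and the randomisation alone and needs no numerical assumption.

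The size of a spurious gain does need one. Under exponential build-up with no dose effect it runs from about 5% to 61% for time constants of 1 to 6 weeks. No single value in that range is an expected size, and with fast onset the gain is negligible. A flat profile would not settle the matter either, but it would hide a dose effect only if a waning effect happened to offset it, and nothing in the document suggests that.

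A reader might infer that the primary result is compromised. It is not: the t-test compares concentrations after the two treatments, and neither it nor the sample size uses the dose claim. The matter should be corrected, but it is confined to a secondary analysis and to one of the reasons given for the treatment duration.

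**What to change.** - **Statistical analysis:** replace the dose-dependence aim of the mixed model with synbiotic-minus-placebo contrasts at week 3 and week 6, from treatment-by-visit terms. Report them as the time course of the effect under the escalation schedule, and state that dose and duration cannot be separated. The model's role in handling missing data stays.
- **Supplement dosing and duration:** remove the dose-dependence aim from the reasons for the 6-week period. The reference to a sustained benefit may stay if it is defined as an effect at week 3 that is still present at week 6, not persistence at a constant dose.
- **If intake data are used:** label any analysis of pill counts or powder weights as non-randomised and exploratory.

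The cost is wording. The dosing schedule, visits, samples, mixed model and primary t-test all stay as they are. The trial gives up a secondary claim that its design cannot support.

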### Target population

The trial will recruit Stage IV-V non-dialyzed CKD patients. Inclusion criteria will include patients under the care of a Nephrologist at the Princess Alexandra Hospital with an estimated glomerular filtration rate (eGFR) between 10-30 ml/min/1.73 m^2^, aged ≥18 years and able to provide informed consent. Patients will be excluded if they meet any of the following criteria: previous renal transplant; receiving/or have received radiation to the bowel or large bowel resection; consumed pre- or probiotics or antibiotic therapy within 1 month of study commencement; medically diagnosed irritable bowel syndrome, Crohn’s disease or ulcerative colitis; non-English speaking; likely to receive a transplant or progress to dialysis within 6 months, as determined by treating physician; severely malnourished (Subjective Global Assessment: C); or having had a clinically significant change to their immunosuppressant dose within 6 months (determined by the medical team). The latter criterion is to mitigate any risk associated with severely immunocompromised patients, although increased risk even in the critically ill is thought to be minimal [20].

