Previous studies in pre-dialysis populations suggest a high incidence of antibiotic prescription secondary to high comorbidity burden, susceptibility to urinary tract infections, and prophylactic use for surgical procedures. Because this is a proof-of-concept study and the use of antibiotics may confound the mechanisms underpinning the synbiotic therapy, sensitivity analyses will be undertaken including and excluding patients prescribed antibiotics during either intervention arm. In addition, further analysis will be undertaken to assess whether there is a treatment order effect. The null hypothesis will be rejected at the 0.05 level. The statistical analyses will be performed using Stata (version 12, 2012, Statacorp, College Station, TX).

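### The antibiotic sensitivity analysis leaves in patients treated only during the washout, an exposure that the entry criterion treats as disqualifying before period 1

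*Protocol article*

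**What the plan says.** All statements are in the Protocol article.

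- **Statistical analysis**, on expected use: "Previous studies in pre-dialysis populations suggest a high incidence of antibiotic prescription". On why it matters: "the use of antibiotics may confound the mechanisms underpinning the synbiotic therapy". On the rule: "sensitivity analyses will be undertaken including and excluding patients prescribed antibiotics during either intervention arm".
- **Target population**: a patient is not eligible who has "consumed pre- or probiotics or antibiotic therapy within 1 month of study commencement". Study commencement is not defined as either the start of run-in or randomisation.
- **Study design**: "Participants will undergo a 2 week run-in period, followed by randomisation to either synbiotic supplements or placebo for 6 weeks"; then "participants will undergo a further 4 week washout period followed by crossover to the alternative intervention". On the length of the washout: "The 4 week washout is considered sufficient for the pre-intervention microbiota to re-establish".
- **Table 2**: the second baseline is at week 11 and the first period ends at week 6, so the gap on that calendar is 5 weeks.
- **Statistical analysis**, primary test: an independent t-test between sequences, with "the difference between serum concentrations measured after the first and second treatment as the dependent variable".

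No section counts antibiotics taken in the washout for the sensitivity analysis.

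**The concern.** The sensitivity analysis has one purpose: to show the treatment effect without a confounder that the plan expects to be common. Its exclusion window follows the dosing calendar and ignores how long an antibiotic may matter. A course that starts on the first day of period 2 removes the patient. A course that ends the day before does not. Nothing in the stated rationale supports drawing the line there.

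The entry criterion shows that the plan regards antibiotics in the preceding month as a problem, even though the first endpoint comes at least 6 weeks after entry. Before period 2 the same exposure is accepted. At stake is how far the excluding analysis can be read as an analysis free of antibiotic confounding. The primary result is not at stake.

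**Working it through.** **1. Windows side by side.**

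| Interval | Length | Antibiotic rule |
|---|---|---|
| Month before study commencement | 1 month | Bars entry |
| Run-in | 2 weeks | Barred only if commencement means randomisation |
| Period 1 | 6 weeks | Excluded in the sensitivity analysis |
| Washout | 4 weeks (text), 5 weeks (Table 2) | None |
| Period 2 | 6 weeks | Excluded in the sensitivity analysis |

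A 4-week washout lies wholly within one month of the period 2 baseline. A 5-week washout does so except for its first few days.

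**2. Share of time not covered.**

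- From randomisation, study text: 4 / (6 + 4 + 6) = 4/16 = 25%.
- From randomisation, Table 2: 5 / (6 + 5 + 6) = 5/17 = 29%.
- With run-in, if commencement means its start: (2 + 4)/18 = 33%, or (2 + 5)/19 = 37%.

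These are shares of time. They are not shares of misclassified patients, because a patient with a further course in a treatment period is excluded anyway.

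**3. Patients affected (illustration).** The article gives no prescribing rate. Assume a constant rate and let r be the share of patients with at least one course in the 12 treatment weeks. Then the weekly rate is λ = −ln(1 − r)/12. Among patients who stay in the excluding set, the share with a washout course is p = 1 − exp(−4λ) = 1 − (1 − r)^(1/3). The expected number among the 24 planned completers is 24 × (1 − r) × p.

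| Assumed r | p | Patients of 24 |
|---|---|---|
| 10% | 3.5% | 0.75 |
| 20% | 7.2% | 1.38 |
| 30% | 11.2% | 1.88 |
| 40% | 15.7% | 2.25 |
| 50% | 20.6% | 2.48 |

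With run-in added (6 weeks), p runs from 5.1% to 29.3%, or 1.11 to 3.51 patients.

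**4. What reaches the treatment estimate.** Assume that the sensitivity analysis repeats the primary t-test. Let τ be the treatment effect, π the period difference, δ an additive antibiotic shift in period 2, and k the fraction of the synbiotic response lost after a washout course. The mean of first minus second value is:

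- synbiotic first: τ + π − pδ;
- placebo first: −τ(1 − pk) + π − pδ.

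Half the difference between sequences is τ(1 − pk/2). The common shift pδ has dropped out. With complete loss of response (k = 1, an assumed extreme), the dilution is p/2, that is 0.035/2 = 1.7% to 0.206/2 = 10.3%. On the planned effect of 0.30 × 14 = 4.2 μmol/L this is about 0.07 to 0.43 μmol/L.

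The shift δ cancels only on average. With n patients per sequence, one more affected patient in one sequence than in the other moves the estimate by δ/(2n): δ/24 at 12 per sequence, and δ/12 if r = 50% leaves 6 per sequence. The size of δ is not known.

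**The case against.** **The look-back is an entry criterion and does not govern the analysis.** This stands. A reader might infer that the plan contradicts itself, but nothing says that the eligibility rule carries over to the sensitivity set. The inconsistency is one of logic, because both rules guard against the same confounder.

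**A washout course disturbs period 2 only, but randomised sequence takes care of that.** This largely stands. A reader might infer a one-sided bias that goes straight into the within-patient difference. The planned test compares that difference between sequences, so an average shift common to both cancels, as shown above. Added variance, chance imbalance and an altered response to the synbiotic do not cancel.

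**The microbiota has recovered by the endpoint.** Even a course ending the day before period 2 precedes the final sample by about 6 weeks, longer than the 4 weeks the plan considers enough for re-establishment. This has some force for the final value. But that statement is about recovery after the study supplement, and the plan does not extend it to antibiotics. The entry look-back also precedes an endpoint at least 6 weeks away, and would serve little purpose if such exposure were harmless by then. The period 2 baseline, the optional fecal sample and the week 14 mid-point value, which bears on the dose-dependence model, come sooner.

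**A third of courses are missed.** A reader might infer this from the 33% to 37%. The documents do not support it: those figures are shares of time and include run-in, which the entry criterion may already cover.

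**Such detail belongs in the full protocol or analysis plan.** It would, had the article left the window open. The article states the window.

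**Conclusion.** The point holds as a rule drawn too narrowly for its own purpose. The washout is uncovered on either meaning of study commencement: 25% of the time from randomisation by the text, 29% by Table 2. Run-in adds to the gap only on one of the two meanings.

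Under assumed rates of 10% to 50% over the 12 treatment weeks, constant in time, and a 4-week washout, roughly 1 to 2.5 of 24 completers would remain in the excluding set after a washout course. Even if all of them lost the whole response to the synbiotic, the average dilution would be about 2% to 10%. Variance and chance imbalance come on top and cannot be sized from the article.

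This is a cheap improvement to a supporting analysis. It does not support a claim that the plan contradicts itself or that the primary analysis is biased.

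**What to change.** - Define the excluding set as patients with no antibiotic from 1 month before each period's baseline to the end of that period. This covers the washout, apart from the first few days if it lasts 5 weeks, and covers run-in whichever meaning of commencement applies.
- State whether study commencement means the start of run-in or randomisation.
- Make sure that the dates of antibiotic courses are available for run-in and washout as well as for the treatment periods. The article does not say how they are recorded, and they may already be.

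The cost is one or two sentences and the exposure dates. The sensitivity set becomes somewhat smaller, by about 1 to 2.5 patients under the assumptions above (up to 3.5 if run-in courses also count). The primary analysis and the sample size do not change.

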## Discussion

This double-blind placebo-controlled randomised cross-over trial has been designed to provide evidence in order to better determine whether synbiotic therapy can reduce serum concentrations of IS and PCS and in turn improve clinical outcomes in CKD. In addition to overcoming suboptimal study design and methodological limitations of previous studies, SYNERGY aims to address the translation of the inflammatory and oxidative mechanisms that are thought to underpin the toxicities of IS and PCS contributing to the high prevalence of premature CVD observed in CKD [60]. More explicitly, *in vitro* studies suggest the pathogenic actions of IS and PCS stem from the induction of reactive oxygen species (ROS), which activate the NF-kB pathway, resulting in both oxidative stress and pro-inflammatory cytokine production [61,62]. Furthermore, treatment with antioxidants and NF-kB inhibitors dose-dependently inhibit the fibrotic and oxidative effects of IS and PCS [5,14,63]. SYNERGY will be one of the first intervention studies to investigate the translation of these mechanisms in the CKD population.

There are a number of other mechanistically plausible benefits of synbiotic therapy in CKD, independent of the effect on IS and PCS reduction, that will be explored in SYNERGY, specifically, endotoxemia, TMAO, QOL, GI symptoms and microbiota form and function.

Endotoxemia, a marker of impaired intestinal barrier function, has been identified across the full spectrum of CKD, with levels of circulating endotoxins increasing with declining kidney function [64]. Some of the factors contributing to this in CKD include the high prevalence of small bowel bacterial overgrowth [65], increased membrane permeability secondary to chronic low grade inflammation [66], and gut edema secondary to fluid overload and ischemic intestinal injury particularly in the dialysis population [64]. The potential benefit of probiotics on intestinal lining integrity has gained recognition recently, with studies in liver disease patients demonstrating a significant reduction in endotoxin levels following synbiotic therapy [67,68]. Some of the mechanisms proposed include enhanced epithelial barrier function via induction of mucin production, blocking of epithelial binding receptors, and strengthening of epithelial tight junctions through increased expression of proteins [69]. It is therefore conceivable that endotoxemia may improve following synbiotic therapy in CKD.

Like IS and PCS, TMAO is a derivative of colonic bacterial fermentation and has recently been identified as a proatherogenic risk factor [70]. Emerging research has demonstrated that TMAO not only promotes atherosclerosis in mice, but raised levels are associated with major adverse cardiac events in humans (n = 2595) [71]. Despite this link between TMAO and atherosclerosis only recently surfacing, increased levels of TMAO in end stage kidney disease and its amenability to gut microbial manipulation has been recognised for decades [72]. Therefore a decrease in serum TMAO is an attractive prospect following synbiotic therapy.

QOL in CKD patients is often compromised with levels of depression associated with declining kidney function [73]. There is a growing body of evidence substantiating the microbiota-gut-brain axis, linking alterations in the gut microbiota with depression [74]. Further, animal studies have demonstrated that both pre- [75] and probiotics [76] have psychotropic effects, suggesting improvements in QOL following synbiotic therapy is a credible hypothesis. In fact, this theory has been supported in a randomised controlled cross-over study where a cohort of 46 participants with CKD stage 3–4 were reported to have a significant improvement in their QOL following probiotic therapy [77].

GI symptoms are increased in CKD compared to the general population. Furthermore, an observational study comparing the CKD population with the general population highlighted significantly worse GI symptom across 5 GI domains (pain, indigestion, constipation, diarrhoea and eating dysfunction) using the GSRS tool [52]. Given the reported benefits of pre- and/or probiotics span across these 5 GI domains [78], GI symptom improvement presents itself as another promising outcome measure in SYNERGY.

The microbiota analysis in this study should help evaluate whether the probiotic strains *per se,* or other alterations in the microbiota of the large bowel, might contribute to these outcomes.

Lastly, the role of diet in serum IS and PCS concentrations is well documented, yet monitoring dietary intake has been a limitation of studies to date [79]. One of the key strengths of SYNERGY that will enhance the rigour of this trial is the multi-method approach to monitoring participants’ dietary intakes throughout the study.

In summary, considering the potential for synbiotics to not only shift toxin levels, but to also impact on CVD and CKD outcomes, there is a need for well designed, intervention studies to establish the effectiveness of this innocuous, low cost therapy. The SYNERGY study aims to provide proof-of-concept data to elucidate whether altering the microbiota in the CKD population is likely to be effective, tolerable and can impede the processes associated with CVD and CKD progression.
